**Methodology:**

The study will be a single-blind parallel-group randomised controlled trial, where baseline data will be collected from 392 estimated antenatal mothers, after that they will be evenly randomised using randomly generated permuted block sizes (each containing two intervention and two control assignments). The study participants will be antenatal mothers of ages 18 years and above who are in third trimesters and attending Federal Medical Centre Gusau, Zamfara State, Nigeria; during the study period and fulfilled all the inclusion and exclusion criteria. The intervention group will undergo five-health education sessions on immunisation, which will be strictly guided by Social Cognitive Theory-based intervention module: while the control group will receive usual care (standard care). Follow-up data will be collected using the same questionnaire at 6-weeks post-delivery, 10-weeks post-delivery and 14-weeks post-delivery. The generalized linear mixed model will be carried-out to determine the overall effect of the intervention after controlling for 14 potential confounding variables. An intention to treat analysis will also be carried-out. Childhood immunisation uptake is the primary outcome while the secondary outcomes are: improved knowledge scores, attitude scores, outcomes expectation, self-efficacy scores, cultural beliefs scores and assumptions on religious regulations scores.

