### Outcomes

The primary outcome for the proposed study is childhood immunisation uptake and the secondary outcomes are: improved knowledge scores, improved attitude scores, improved outcomes expectation scores, improved self-efficacy scores, improved cultural beliefs scores and improved assumptions of religious regulations scores. They will be taken at 6 weeks post-delivery, 10 weeks post-delivery and 14 weeks post-delivery *(Refer to S3 File).*

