In order to determine within-group differences with time for knowledge scores, attitude scores, outcome expectation scores, self-efficacy scores, cultural beliefs scores and assumptions of religious regulations scores the researcher will conduct one-way repeated measures analysis of variance (ANOVA) for these variables if there is no substantial non-normality of the residuals. Intention-to-treat analysis (ITT) will be carried-out separately for each group and replacement of missing data will be done through using multiple imputations technique. The estimated outputs that will be obtained after ITT analysis will then be pooled into a single data set, after that, the Generalized Linear Mixed Models (GLMM) analysis will be carried-out to investigate the overall effectiveness of the intervention using 95% Confidence Interval (CI) and 0.05 will be set as the level of significance. Two measures of effect size will be used in this study: Partial Eta squared and the coefficients of the fixed effects. Partial Eta squared will be used in the mixed design repeated measures ANOVA, and will be classified as small, medium or large effect (0.2, 0.5 and 0.8) respectively according to the magnitude. The coefficients of the fixed effects will be used in the GLMM analysis.

In order to check the robustness of the result, sensitivity analysis will be performed to determine the effect of drop out and non-response on the findings of the proposed study, the GLMM analysis will be repeated again without replacing the missing values. The differences between the coefficients obtained after replacement (intention to treat analysis) and before replacement of the missing values (per-protocol) will then be calculated and expressed as percentages of the former.

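### As written, multiply imputed outputs are pooled into one data set before a single GLMM is run, so between-imputation variance is lost and confidence intervals can be too narrow

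*Protocol article*

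**What the plan says.** The Data analyses section of the protocol article sets out a sequence:

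- The intention-to-treat step is "carried-out separately for each group and replacement of missing data will be done through using multiple imputations technique".
- Next, "The estimated outputs that will be obtained after ITT analysis will then be pooled into a single data set".
- The model comes last: "after that, the Generalized Linear Mixed Models (GLMM) analysis will be carried-out to investigate the overall effectiveness of the intervention". Its result is to be given with a 95% interval and tested at 0.05.
- As a sensitivity analysis, "the GLMM analysis will be repeated again without replacing the missing values". The two sets of coefficients are compared as a percentage difference. Standard errors, intervals and p-values are not compared.

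The abstract gives the GLMM its role: "The generalized linear mixed model will be carried-out to determine the overall effect of the intervention after controlling for 14 potential confounding variables". The Outcomes section says: "The primary outcome for the proposed study is childhood immunisation uptake". The article does not call the GLMM primary, but it describes no other test of the intervention effect on uptake. The chi-squared tests are for baseline comparisons, and the t-tests and repeated measures ANOVA are for the scores.

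**The concern.** Multiple imputation is valid because the model is fitted in every completed data set and the estimates are combined afterwards. The spread of estimates between imputations carries the uncertainty about the missing values. The article reverses the order: it pools data first and fits the model second. One data set gives one coefficient and one standard error, so there is no between-imputation spread to add. Imputed values then count as if they had been observed, and in stacked files each woman is counted once per imputation.

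At stake are the interval and p-value of the overall-effectiveness analysis. The planned sensitivity analysis would not expose the fault, because coefficients can agree closely while the standard errors differ.

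**Working it through.** The plan has no figure of its own on this point to reproduce. The planned 196 per group has no bearing on it.

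**Inputs from the article.** 382 women randomised equally, so 191 per arm (Study process); imputation by group; alpha 0.05, taken as two-sided.

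**Assumed, because the article does not give them.** Fraction missing f of 10%, 20% or 30%, completely at random; number of imputations M of 5 or 20; true uptake of 20%, 25% or 50%; no true effect; a difference in proportions at one time point in place of the repeated-measures GLMM with 14 covariates.

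**Step 1: what the correct method needs.** With coefficient Q and variance U from each of M fits, Rubin's rules give the variance T = mean(U) + (1 + 1/M)B, where B is the variance of Q between imputations. A single fit gives no B.

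**Step 2: approximate size by formula.** Let V = 2σ²/n be the variance of the difference with complete data. Then B = V·f/(1−f), and the true variance of the averaged estimate is about V/(1−f) for large M. The ratio of reported to true standard error is:

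- averaged, fractions kept: reported variance is about V(1−f), so the ratio is 1−f;
- one completed file: reported variance V, true variance V(1+f)/(1−f), so the ratio is √[(1−f)/(1+f)];
- stacked: reported variance V/M, so the ratio is about √[(1−f)/M].

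Type I error is 2[1 − Φ(1.96 × ratio)].

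| Handling | f = 10% | f = 20% | f = 30% |
|---|---|---|---|
| Averaged: ratio, type I error | 0.90, 7.8% | 0.80, 11.7% | 0.70, 17.0% |
| One file: ratio, type I error | 0.90, 7.6% | 0.82, 11.0% | 0.73, 15.0% |
| Stacked, M = 5: ratio, type I error | 0.42, 41% | 0.40, 43% | 0.37, 46% |
| Stacked, M = 20: ratio, type I error | 0.21, 68% | 0.20, 70% | 0.19, 71% |

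In numbers, at 20% uptake √V = √(2 × 0.2 × 0.8/191) = 0.0409. With f = 20%, the averaged file reports 0.0409 × √0.8 = 0.0366 against a true 0.0409/√0.8 = 0.0458.

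At f = 5% the averaged ratio is 0.95 and the type I error is 2[1 − Φ(1.862)] = 6.3%.

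**Step 3: simulation** (binary uptake, M = 20, 6,000 runs, imputation by arm).

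| Handling | Uptake 20%: f = 10 / 20 / 30% | Uptake 50%: f = 10 / 20 / 30% |
|---|---|---|
| Rubin's rules | 0.049 / 0.051 / 0.047 | 0.052 / 0.052 / 0.053 |
| Averaged, fractions kept | 0.080 / 0.120 / 0.169 | 0.075 / 0.115 / 0.177 |
| One completed file | 0.080 / 0.114 / 0.156 | 0.068 / 0.106 / 0.148 |
| Stacked | 0.678 / 0.694 / 0.715 | 0.678 / 0.697 / 0.725 |
| Averaged, rounded to 0/1 | 0.053 / 0.054 / 0.054 | 0.143 / 0.255 / 0.374 |
| No imputation | 0.051 / 0.051 / 0.047 | 0.049 / 0.052 / 0.053 |

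With M = 5 and 25% uptake, averaging and rounding gives 8.0% / 11.2% / 15.6%. Stacking with M = 5 gives 40–49%. A score outcome (assumed baseline correlation 0.5, M = 5) gives 7.7% / 12.3% / 16.2% when averaged; at 20% missing its reported standard error is 0.081 against a true 0.103. At 5% missing, simulated averaging gives about 5.7–6.6%.

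The rounded row needs care. At 20% uptake the false-positive rate stays near 5%, yet at f = 20% the standard error is 0.0375 against 0.0458 by Rubin's rules. Rounding pulls nearly all imputed values to not immunised, which shrinks the estimated difference along with its spread. At 50% uptake the same rule gives 14–37%.

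**The case against.** The strongest answer is that pooling here may only mean joining the two arms. Imputation is done separately by group, and a between-arm model cannot be fitted until the arm files are merged. That step is necessary and harmless, and the way estimates are combined afterwards is a detail that an article may leave to an analysis plan. The reading is plausible, but it does not rescue the sentence. Merging arms within imputations leaves as many data sets as there are imputations. The text ends with one, fits the GLMM to it, and mentions no combining step. It states a procedure and is not merely silent.

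Second, a reader might infer that false positives are inflated however the pooling is done. The calculations do not support that: binary uptake averaged and rounded at a low rate with 20 imputations stays near 5%, and with little missing data averaging costs little.

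Third, the GLMM without imputation counts no imputed value as observed, and under the assumptions above its error rate is about 5%. This is a real but partial safeguard. It is a sensitivity analysis, and the planned comparison covers coefficients only.

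Fourth, the size is not fixed by the article and the simulations simplify the GLMM. Both points stand, so the figures are ranges under assumptions.

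**Conclusion.** The sentence is wrong as written and should be corrected before the analysis. It prescribes pooling of data, then one GLMM, with no later combination across imputations. Followed literally, it drops the between-imputation variance and gives intervals that are too narrow. Under an assumed 10–30% missing, type I error is about 8–18% for averaged files and 40–70% or more for stacked files, against about 5% with Rubin's rules. The inflation is small at 5% missing or below unless files are stacked. For uptake averaged and rounded at low rates, the false-positive rate can stay near 5%, although the interval is still narrower than it should be.

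A reader might go further and conclude that the trial's effectiveness result will certainly be invalid, or by a known amount. The article does not support that. It does not say how the imputations are to be collapsed, how many there are, or how much data will be missing, and the authors may have meant only to merge the arms.

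**What to change.** Replace the pooling sentence in Data analyses with, for example:

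> Missing outcomes are multiply imputed by arm; the arms are merged within each imputation; the GLMM is fitted in each imputed data set, and coefficients and standard errors are combined by Rubin's rules; all randomised women are analysed in the arm allocated.

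The last clause also separates intention to treat, which concerns who is analysed and in which arm, from the handling of missing values. The number of imputations is for the trial statistician to choose.

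The cost is one sentence, slightly more computing, and intervals that are wider but correct. No trial procedure changes. According to Study process, follow-up was still to come, and the Protocol amendments section already provides for communicating changes to the analysis.

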### Sample size determination

The minimum sample size required to test the proposed study hypotheses has been determined using the formula for comparing two proportions in selected samples of both intervention and control groups [57]. This formula gave the required number (n) for each group. This provided a total sample size of 196 participants in each group, which will then be multiplied by two since the study is comprised of two arms. Therefore, 392 are the calculated sample size required to test the hypothesis for this study *(Refer to S1 File).*

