### Study process

An illustration of the study process was done in accordance with CONSORT statement [55]. During the eight weeks recruitment period, a total of 551 pregnant women had been assessed for possible inclusion in the study out of which 159 did not meet the inclusion criteria while ten declined to participate. The remaining three hundred and eighty-two participants were then randomly assigned equally, to either the intervention or the control group. SPIRIT schedule of the study and flow diagram of the study are shown in Figs 1 and 2 respectively. The baseline data of the study participants has been taken and they will both be followed up at 6 weeks post-delivery, 10 weeks post-delivery and 14 weeks post-delivery to assess the effect of the intervention regarding their knowledge, attitude, outcome expectations, self-efficacy, cultural beliefs and assumptions of religious regulations towards child immunization, as well as to assess their child immunization uptake.

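### Partial eta squared is graded at 0.2, 0.5 and 0.8, the cut-offs for a standardised mean difference, so the effect-size labels for the six secondary scores will tend to be too low

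*Protocol article*

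**What the plan says.** The Data analyses section of the protocol article names the effect sizes: "Two measures of effect size will be used in this study: Partial Eta squared and the coefficients of the fixed effects". It places the first of them in a particular analysis, "Partial Eta squared will be used in the mixed design repeated measures ANOVA", and in the same sentence says that it "will be classified as small, medium or large effect (0.2, 0.5 and 0.8) respectively according to the magnitude". The fixed-effect coefficients are assigned to the generalized linear mixed model and are not graded.

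No standardised mean difference is planned anywhere in the article, so the three cut-offs have no other measure to belong to. No source or reason is given for them.

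The outcomes graded in this way are the six secondary scores: knowledge, attitude, outcome expectation, self-efficacy, cultural beliefs and assumptions on religious regulations. The Outcomes section sets the post-delivery visits: "They will be taken at 6 weeks post-delivery, 10 weeks post-delivery and 14 weeks post-delivery".

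**The concern.** The values 0.2, 0.5 and 0.8 are the familiar small, medium and large grades of Cohen's d, a difference between means divided by the standard deviation, which has no upper limit. Partial eta squared is a share of variance and cannot exceed 1. The plan has put the ruler of the first measure against the second.

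At stake is how the secondary results will be described. The effect on these scores is the first of the two research questions in the Background section, and the same section says the findings may inform policy makers. A pre-specified rule that calls a conventionally large effect small, or gives it no grade at all, would understate what the intervention did. Replacing the rule after the results are known would look post hoc.

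**Working it through.** **Inputs**
- Measure and cut-offs: partial eta squared at 0.2, 0.5 and 0.8 (Data analyses).
- Allocation: 1:1. The Study process section says "The remaining three hundred and eighty-two participants were then randomly assigned equally, to either the intervention or the control group", so 382 / 2 = 191 per arm.
- Visits: baseline plus three after delivery (Outcomes and Study process).
- Within-person correlation, rho: not given. Assumed equal between all pairs of visits and varied from 0 to 0.9.

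The cut-offs are a grading convention, not a calculated quantity, so there is no figure of the plan's to reproduce.

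**Step 1. Two equal arms, one between-subject comparison**

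eta² = d² / (d² + 4), and in reverse d = 2 × √(eta² / (1 − eta²)).

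| d | eta² |
|---|---|
| 0.2 | 0.04 / 4.04 = 0.0099 |
| 0.5 | 0.25 / 4.25 = 0.0588 |
| 0.8 | 0.64 / 4.64 = 0.1379 |

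| Plan's cut-off for eta² | d needed |
|---|---|
| 0.2 | 2 × √0.25 = 1.0 |
| 0.5 | 2 × √1 = 2.0 |
| 0.8 | 2 × √4 = 4.0 |

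The first table gives the usual 0.01, 0.06 and 0.14 grades for eta squared. All three values lie below the plan's lowest cut-off. A simulation of 4,000 trials with 191 per arm and d = 0.8 gave a mean eta squared of 0.139, below 0.2 in 96% of runs.

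**Step 2. The mixed design, with d = 0.8**

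*(a) Arm main effect over the three post-delivery visits.* The standardised difference of the three-visit mean satisfies d*² = 0.64 × 3 / (1 + 2 × rho), and partial eta² = d*² / (d*² + 4).

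*(b) Arm main effect over four visits, with no difference at baseline.* The average difference is 0.6, so d*² = 0.36 × 4 / (1 + 3 × rho), with the same conversion.

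*(c) Arm-by-time interaction over four visits, with differences 0, 0.8, 0.8 and 0.8.* The deviations from the mean of 0.6 are −0.6, 0.2, 0.2 and 0.2. Their squares sum to 0.48, and 0.48 / 4 = 0.12. Then partial eta² = 0.12 / (0.12 + 3 × (1 − rho)).

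| rho | (a) main, 3 visits | (b) main, 4 visits | (c) interaction |
|---|---|---|---|
| 0 | 0.324 | 0.265 | 0.039 |
| 0.3 | 0.231 | 0.159 | 0.054 |
| 0.5 | 0.194 | 0.126 | 0.074 |
| 0.7 | 0.167 | 0.104 | 0.118 |
| 0.9 | 0.146 | 0.089 | 0.286 |

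Four of the fifteen entries pass 0.2 and would be labelled small. The other eleven fall below small. None reaches the medium cut-off of 0.5.

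**Step 3. The two sets of labels compared directly**

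| Partial eta² | At 0.01 / 0.06 / 0.14 | At the plan's 0.2 / 0.5 / 0.8 |
|---|---|---|
| below 0.01 | below small | below small |
| 0.01 to 0.06 | small | below small |
| 0.06 to 0.14 | medium | below small |
| 0.14 to 0.2 | large | below small |
| 0.2 to 0.5 | large | small |
| 0.5 to 0.8 | large | medium |
| 0.8 or more | large | large |

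The plan's label is lower for every value from 0.01 up to 0.8, and it is never higher.

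**The case against.** The strongest reply is that little hangs on this. The error touches a verbal label on a supplementary statistic for secondary outcomes. Overall effectiveness is judged by the generalized linear mixed model with its 95% confidence interval, where "0.05 will be set as the level of significance", and the effect measure there is the fixed-effect coefficient. Childhood immunisation uptake, the primary outcome, is not graded by these cut-offs. All of this stands, and it limits the weight of the point.

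Four stronger readings are tempting, and the document does not support them.

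- *Every large effect will be reported as less than small.* This is too absolute. With d = 0.8 the arm main effect passes 0.2 at low correlation and the interaction passes it at high correlation. In a simple two-arm comparison any d above 1.0 passes. Such effects would be called small, which is still too low but is not below small.
- *All six labels will be wrong.* That depends on the results. A partial eta squared below 0.01 is below small on either scale.
- *The plan contradicts itself on which ANOVA supplies the measure.* The Data analyses section uses one-way repeated measures ANOVA for changes within each arm, but it never attaches partial eta squared to that analysis. It attaches it to the mixed design, which does contain arm and arm-by-time terms. At most, the mixed ANOVA is named without being introduced, which a condensed article may leave to the full protocol.
- *0.01, 0.06 and 0.14 would be exact here.* They match d only in the simple two-arm case. In the table above, an interaction with d = 0.8 gives 0.039 to 0.054 at correlations of 0 to 0.3, which those cut-offs would also call small. They are the right convention for the measure, not an exact translation for every term.

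**Conclusion.** The grading rule is wrong as written: it applies the cut-offs of a standardised mean difference to a proportion of variance. Whenever partial eta squared lies between 0.01 and 0.8, the label is lower than the usual convention for that measure would give. For a plain between-arm comparison the plan's 'large' needs arms four standard deviations apart. In the mixed design, a d of 0.8 is graded at most small and often below it.

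The mixed-design figures rest on assumptions: equal correlation between visits, a correlation between 0 and 0.9, and an effect of constant size after delivery. The mismatch of scales depends on none of these.

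Severity is minor to moderate. The labels for the six secondary scores would be systematically too low. The primary uptake analysis, the significance tests, the mixed-model coefficients and the planned 196 per group are unaffected.

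**What to change.** Amend the sentence in the Data analyses section in one of two ways:

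1. Keep partial eta squared and grade it at 0.01, 0.06 and 0.14.
2. Keep 0.2, 0.5 and 0.8, but apply them to a between-arm standardised mean difference reported with its 95% CI.

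Under either option, state which term of the mixed design ANOVA is graded, for example arm by time, because the value differs widely between terms.

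The first option costs one sentence. The second adds a quantity that can be computed from data already to be collected. Neither changes data collection, the tests or the sample size. By the article's account baseline data have been taken and follow-up lies ahead, so the change should be recorded before the scores are analysed. The Protocol amendments section already provides the route for notifying a change to the analysis.

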#### Study pro forma

The researcher designed a study hand cards which will be used to collect information about childhood immunization uptake. The hand cards will be given immediately after recruitment, and will be submitted to the researcher at three months post-delivery after Penta 3 uptake. The card has participant’s serial number, basic bio-data, and a short appeal to the attending physician or nurse, informing them that the patient is enrolling into a follow-up study, and his/her help is needed to kindly fill the blanks provided on the card. The items it contained are: childhood immunization uptake and date given (BCG, Hep B-0 and OPV-0; OPV-1, PCV-1 and Penta-1; OPV-2, PCV-2 and Penta-2; OPV-3, PCV-3 and Penta-3).

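### The only effect measure planned for uptake, the primary outcome, is a mixed-model coefficient, which is not on the scale of the difference in proportions used to size the trial

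*Protocol article*

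**What the plan says.** - **Effect measures.** The Data analyses section limits them to two: "Two measures of effect size will be used in this study: Partial Eta squared and the coefficients of the fixed effects". Partial eta squared is tied to the repeated-measures ANOVA. For the mixed model, "The coefficients of the fixed effects will be used in the GLMM analysis". The t-tests and the ANOVA are assigned by name to the six scores, so the mixed model is the only outcome analysis left for uptake.
- **Robustness check.** The same section refits the mixed model without imputation. The differences between the two sets of coefficients "will then be calculated and expressed as percentages of the former", that is, of the coefficients after imputation.
- **Outcome.** Under Outcomes, "The primary outcome for the proposed study is childhood immunisation uptake". Of the outcomes together it says: "They will be taken at 6 weeks post-delivery, 10 weeks post-delivery and 14 weeks post-delivery". The Study pro forma section records uptake as an ordered series: "OPV-1, PCV-1 and Penta-1; OPV-2, PCV-2 and Penta-2; OPV-3, PCV-3 and Penta-3". The Background gives 6, 10 and 14 weeks as the ages at which doses 1, 2 and 3 are due.
- **Sizing.** The Sample size determination section reached 196 per group "using the formula for comparing two proportions in selected samples of both intervention and control groups".
- **Not stated.** The article gives no link, distribution, random effects or estimation method for the mixed model.

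**The concern.** The trial was sized on a difference between two proportions, and the two earlier trials that the Background uses for comparison are reported as proportions. The effect measure planned for uptake is of another kind. In a logit model with a random effect per woman, the group coefficient compares odds for women who share the same random effect. For a given difference in proportions, its absolute size grows with the variance of that random effect.

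Ordered doses sharpen this. If uptake is scored at each visit, and a later dose presupposes the earlier one, each child's three values are nearly nested. The between-woman variance is then estimated as very large, and the coefficient moves with it.

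At stake are the reported size of the effect and the robustness check. The Background names policy makers as readers, and they need the gain in uptake. A percentage change in the coefficient mixes a change in effect with a change in scale.

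**Working it through.** **1. The plan's own figure.** The inputs behind 196 per group are in a supplementary file that is not shown, so 196 can only be tested for compatibility. Take 33% v 20% (third dose, cited Nigerian community trial), two-sided 0.05 and 80% power:
- pooled formula: 180 per group
- pooled with continuity correction: 195
- unpooled: 177, and 177/0.9 = 197 with 10% dropout

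So 196 is compatible with a difference of 0.13. This does not show that 0.13 was the basis.

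**2. The effect on the scale of proportions.** At 33% v 20%:
- risk difference = 0.33 − 0.20 = 0.13
- risk ratio = 0.33/0.20 = 1.65
- marginal odds ratio = (0.33/0.67)/(0.20/0.80) = 1.97, log odds ratio 0.68
- with 191 per arm (382 randomised, Study process section), SE = √[(0.33×0.67 + 0.20×0.80)/191] = 0.0447, so the 95% CI for the difference is about 4.2 to 21.8 points

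**3. The coefficient when uptake is scored at each visit.** Inputs: control 25/22.5/20%, intervention 35/34/33%. The first and third values come from the cited trial; the middle ones are assumed. Only the patterns 000, 100, 110 and 111 occur, with 191 per arm. Model: logit P(uptake) = visit effect + β × group + u, with u normal, mean 0 and standard deviation (SD) σ. Maximising over the visit effects and β at fixed σ:

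| σ | β | minus log-likelihood |
|---|---|---|
| 1 | 0.70 | 546.1 |
| 5 | 1.91 | 335.5 |
| 20 | 6.75 | 287.8 |
| 55 | 18.2 | 281.6 |
| 90 | 29.7 | 281.0 |

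The fit improves at every step and β grows with σ. Only the ratio settles (29.7/90 = 0.33), so there is no finite maximum-likelihood value. With 196 per arm the same behaviour continued to σ = 160.

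**4. Dependence on the fitting method** (same rates, ordered data).
- Gauss-Hermite integration, 196 per arm: β = 0.31 with 5 to 15 nodes, 18.3 with 25 and 19.8 with 50.
- Penalised quasi-likelihood: finite. The median odds ratio over 20 simulated trials was 2.1 (SD about 2.5). A fit to expected counts with 196 per arm gave β = 0.84, or exp(0.84) = 2.3.

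**5. Dependence on out-of-order records** (191 per arm, visit values flipped independently). Flipping a fraction f shrinks the true difference to 13 × (1 − 2f) points.

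| Records flipped | 14-week difference (points) | Odds ratio, full maximum likelihood |
|---|---|---|
| 2% | 12.5 | 36 |
| 5% | 11.7 | 5.5 |
| 10% | 10.4 | 2.4 |

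**6. The robustness percentage under quasi-likelihood.** With 0, 5 and 10% flipped, β was 0.82, 0.63 and 0.50, which is −23% and −39%. The risk difference changed from 13.0 to 11.7 and 10.4 points, or −10% and −20%. The coefficient shows about twice the relative change. This used flipped observed records, not actual imputation.

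**7. The test.** In 400 null simulations for each of three uptake profiles, rejection was 7.2%, 4.8% and 5.8%. The simulation error is √(0.05 × 0.95/400) = 1.1 points.

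**The case against.** The strongest reply is that the unbounded estimate belongs to a model that the article does not specify. It needs a logit link, a random intercept per woman, full maximum likelihood, and one nested yes/no value per visit. An analysis plan commonly settles such details. That stands. A reader might infer from the tables above that the planned coefficient has no stable value, or that the published effect will be grossly overstated. The documents do not support either as a general statement. In 40 simulated trials per setting with 0, 1, 2, 5 and 10% of records flipped, quasi-likelihood always converged, with median odds ratios of 2.2, 2.3, 2.1, 1.9 and 1.7 against a marginal 1.97. Part of that decline is genuine dilution.

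A single completion status per child is also a possible reading. The hand card is returned once, after the third dose, and the sizing compares two proportions. The instability would then not arise. The Outcomes section lists three times, so both readings remain open.

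The large odds ratios also depend on what counts as out of order. When 1, 2, 5 or 10% of children, rather than visit records, were given a non-nested pattern (196 per arm), β was 9.0, 6.5, 3.8 and 2.3. Neither set forecasts this trial.

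The Data analyses section does plan frequencies and percentages for categorical data. That is description, without a between-arm estimate or a confidence interval. Sizing on proportions and reporting an odds ratio is common, and the null hypothesis is the same.

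What the reply does not remove is the closed list of two effect measures. That is a stated choice, and it leaves the primary outcome without an estimate on the scale of the sizing.

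**Conclusion.** The concern holds in a limited form. As written, the fixed-effect coefficient is the only effect measure that can apply to uptake. Under a logit mixed model it is a woman-specific log odds ratio, not the difference in proportions on which the trial was sized. That mismatch remains for a logit coefficient even if uptake is one status per child.

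The size of the problem is conditional. With uptake scored at each visit and strictly ordered doses, a 13-point gain (marginal odds ratio 1.97) appears as an odds ratio of about 2.1 under quasi-likelihood and has no finite value under full maximum likelihood. The printed coefficient, and the percentage change in it, can therefore reflect the fitting method and a few irregular records. Harm to the robustness check is plausible but was not shown with real imputation, since an imputation model need not break the dose order.

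The test is not in question: false-positive rates were near nominal. The assumptions are the cited trial's rates, an assumed middle dose, a random-intercept logit and visit-level scoring. This is a cheap improvement, not a defect that invalidates the analysis.

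**What to change.** In the Data analyses section, name a population-averaged effect for uptake:

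- Report the uptake proportion per arm, the risk difference and the risk ratio, each with a 95% CI, at 14 weeks, and at each visit if uptake is analysed by visit.
- Obtain them from a marginal binomial model with robust standard errors (for example GEE), or by averaging model predictions over all randomised women.
- Express the comparison with and without imputation as a change in percentage points of the risk difference.
- The mixed-model coefficient may stay as a supplement for uptake, and for the six scores.

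The cost is a few sentences and one extra model run, with no new data. The downside is that GEE without imputation needs a stronger missing-data assumption than a likelihood-based mixed model. The planned imputed analysis covers this in part.
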